## Abstract

**Background:**

People with diabetes find it difficult to sustain adequate self-management behaviour. Self-Management Support strategies, including the use of mobile technology, have shown potential benefit. This study evaluates the effectiveness of a mobile phone support intervention on top of an existing strategy in three countries, DR Congo, Cambodia and the Philippines to improve health outcomes, access to care and enablement of people with diabetes, with 480 people with diabetes in each country who are randomised to either standard support or to the intervention.

**Design/methods:**

The study consists of three sub-studies with a similar design in three countries to be independently implemented and analysed. The design is a two-arm Randomised Controlled Trial, in which a total of 480 adults with diabetes participating in an existing DSME programme will be randomly allocated to either usual care in the existing programme or to usual care plus a mobile phone self-management support intervention. Participants in both arms complete assessments at baseline, one year and two years after inclusion.

Glycosylated haemoglobin blood pressure, height, weight, waist circumference will be measured. Individual interviews will be conducted to determine the patients’ assessment of chronic illness care, degree of self-enablement, and access to care before implementation of the intervention, at intermediate moments and at the end of the study.

Analyses of quantitative data including assessment of differences in changes in outcomes between the intervention and usual care group will be done. A probability of <0.05 is considered statistically significant. Outcome indicators will be plotted over time. All data are analysed for confounding and interaction in multivariate regression analyses taking potential clustering effects into account.

Differences in outcome measures will be analysed per country and realistic evaluation to assess processes and context factors that influence implementation in order to understand why it works, for whom, under which circumstances. A costing study will be performed.

**Discussion:**

The intervention addresses the problem that the greater part of diabetes management takes place without external support and that many challenges, unforeseen problems and questions occur at moments in between scheduled contacts with the support system, by exploiting communication technology.

**Trial registration:**

ISRCTN86247213

## Background

Diabetes Self-Management Education (DSME) is defined as “the on-going process of facilitating the knowledge, skills, and ability necessary for diabetes self-care”. The overall objectives are “to support informed decision making, self-care behaviours, problem solving and active collaboration within the health care team and to improve clinical outcomes, health status and quality of life” [1]. Literature shows that it is difficult for patients to stay motivated to sustain self-management behaviour and that most patients need on-going support [2]. Owing to the chronicity of the condition, many challenges, unforeseen problems and questions occur at the ‘in-between moments’ outside the contacts with the health care providers [3]. Diabetes Self-Management Support (DSMS) is defined as “activities to assist people with diabetes to implement and sustain the on-going behaviours needed to manage their illness. It includes activities such as education, reminders and behavioural support” [1]. The implementation of DSME and DSMS strategies and its potential positive effects have been described mostly in sophisticated health care settings in high income countries [4-8]. These programmes use a mix of tools to reach patients, such as written information, phone calls and short messaging services and visits. Mobile technology can be particularly beneficial for the management of a chronic disease like diabetes, for instance by supporting behavioural change and reminders for taking medication and for appointments with care providers [9-11]. Overall, the evidence on the feasibility and advantages of the use of mobile technology is positive, but many studies are small and evidence on its effectiveness is not very robust [12-16]. Despite a growing number of studies about mobile phone applications in low income countries [17,18], we are aware of only one publication about a feasibility study assessing the use of mobile phones for diabetes support in such context. This study showed the feasibility of mobile phone use for peer support and health messaging. The participants reported positive effects of the intervention, for instance increased social support coping, yet their physical parameters did not improve in the 6 months’ follow-up [19]. The literature on the use of mobile technology for supporting self-management also points out the need for more process evaluation in order to better understand under which conditions and why such interventions work.

This study will address these gaps, by evaluating the effectiveness of a mobile phone DSMS intervention on top of an existing DSME strategy in DR Congo, Cambodia and the Philippines, using a randomised controlled design with a follow-up of 24 months. The project aims to evaluate not only the effectiveness of the intervention in each country, but also to assess the processes and contextual factors that influence the implementation of mobile phone technology for supporting self-management in order to understand how it works, for whom, under which circumstances.

## Methods

### Objectives

The primary aim of this study is to evaluate the effectiveness of a mobile phone DSMS intervention in addition to an existing DSME strategy in three countries, Democratic Republic of Congo (DRC), Cambodia and the Philippines, to improve health outcomes (HemoglobinA1C (HbA1C) level, blood pressure, Body Mass Index (BMI), waist circumference and diabetic foot problems), access to care (failure-to-attend rate, perceived quality of care and health care expenditure) and enablement (knowledge, self-management and feeling of coping) of people with diabetes participating in a diabetes self- management education programme. The secondary aim is to identify barriers and facilitating factors, including additional cost via an incremental cost effectiveness analysis, for the implementation of mobile phone technology for supporting self-management in low-to-middle income countries.

### Study design

The study consists of three sub-studies with a similar design in three low-to-middle income countries, which will be independently implemented and analysed. The design is a two-arm Randomised Controlled Trial (RCT), in which a total of 480 adults with diabetes (type 2 or 1) participating in an existing DSME programme in each country, will be randomly allocated to either self-management education as provided by the existing programme (usual care)or to self-management education plus a mobile phone self-management support intervention. Participants in both arms complete assessments at baseline, one year and two years after inclusion.

### Ethical approval

Medical ethical approval for this study was obtained from the Institutional Review Board of the Institute of Tropical Medicine Antwerp (11245776), the Medical Ethics Committee of the *Universitair Ziekenhuis Antwerpen* (B300201111924), the National Ethics Committee for Health Research in Cambodia (207 NECHR), the University of Kinshasa in the Democratic Republic of Congo (ESP/CE/050/11) and the Veterans Memorial Medical Centre in the Philippines (VMMC-2011-012).

### Study context and population

The target population consists of persons with diabetes who are presently participating in existing DSME programmes in the DRC, Cambodia and the Philippines. The overall prevalence of diabetes in DRC is estimated between 3.2%, in Cambodia at 2.9% and in the Philippines at 10.0% (IDF [20,21]). These existing DSME programmes have been developed in reaction to their surrounding health system and its wider social, cultural and economic context [22,23]. To some extent, the three DSME programmes could be explained as exemplary for their context.

In DRC, the study context is an established network of 60 primary care first line centres for diabetes care in Kinshasa, in which specialised nurses, referred to as educators, act to implement the DSME programme. Five centres have been purposively selected to recruit study participants. Similar to other countries in Sub-Saharan Africa, professional care for people with diabetes is usually provided at health services [24,25]. The DSME programme in the Philippines is provided by a number of specially trained ‘Barangay’ or community health workers and/or nursing aides/midwives as educators in Quezon City (Metro Manila), in the City of Batac (Ilocos Norte Province) and in the municipality of Pagudpud (Ilocos Norte Province). Health systems in Asian countries have a long-standing tradition of such community health workers in the delivery of primary care. The DSME programme in Cambodia is facilitated through community-based peer educator networks, which began in 2005 as a relatively new development. Peer educators are responsible for the DSME programme for patients who live in their area, supported by a headquarter office in Phnom Penh. Nine peer educators have been purposively selected from one urban network and 6 rural networks in 2 provinces (Kampong Speu province, Takeo province).

Because of differences in the existing DSME programmes in each country, the numbers of diabetics cared for by one educator are different in DR Congo, Cambodia and the Philippines. The purposive selection of participating centres in each country is based upon comparable patient size, quality of DSME programme, willingness of DSME programme staff to be part of a research project and convenience factors such as travel distance. Figure 1 shows how the design is implemented in each country.

**Figure 1 F1:**
[figure not shown]
Context, study sites and block randomisation of the TEXTFORDSM study.

### Sample size calculation

The primary outcome measure on which the sample size calculation is based is the difference in the proportion of diabetics with a well controlled HbA1C (defined as HbA1C <53 mmol/mol - comparable with 7.0% [26]) between the intervention and the usual care group. We consider a difference in HbA1C of 15% between the intervention and the usual care group after 24 months as relevant and we assume that at the start of the intervention, 60% of the participants has a well-controlled HbA1c. Unlike most interventions reporting results in terms of decrease in mean HbA1C levels [27], we chose our outcome parameter at group level (% of people with well controlled HbA1C), because this is more relevant from a program perspective. There is very little information about the current levels of HbA1C control in cohorts of people with diabetes either in Africa or in Asia [28,29]. We based our assumption on a study from China, in which 60% of people with diabetes in a hospital cohort had well controlled HbA1C levels [30]. To reach a 2-sided significance level of 5% with 80% power, and adjusting for 10% drop-out rate, the trial needs 240 participants in each arm (intervention and control group), meaning a total of 480 study participants – in each country.

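### The stated sample-size inputs do not give 240 per arm: at 80% power they give 169 to 184, and the document does not show which element is misstated

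*Protocol article*

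**What the plan says.** All the ingredients stand in the Sample size calculation section of the protocol article.

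- **Measure:** "the difference in the proportion of diabetics with a well controlled HbA1C" between the two arms, with control defined as HbA1c below 53 mmol/mol.
- **Effect:** "We consider a difference in HbA1C of 15% between the intervention and the usual care group after 24 months as relevant".
- **Reference level:** "we assume that at the start of the intervention, 60% of the participants has a well-controlled HbA1c".
- **Error rates, attrition and result:** "To reach a 2-sided significance level of 5% with 80% power, and adjusting for 10% drop-out rate, the trial needs 240 participants" in each arm, which makes 480 in each country.

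The section mentions no continuity correction, design effect, multiplicity adjustment or other inflation. The Study design section describes three country sub-studies "which will be independently implemented and analysed". The Data analyses section tests the primary endpoint at a two-sided 5% level and mentions clustering only as a matter for the analysis.

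**The concern.** The section sets out a complete calculation, so a reader should be able to repeat it and arrive at 240. The result is well above what the inputs require, and the gap is too large for rounding or for the choice among the usual formulas. At least one element is therefore misstated or left out: the power, the significance level, or an inflation factor.

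The figure serves each of the three sub-studies. If no inflation was used, readers will take each one as designed for 80% power when its size gives about 90%, and will weigh a null result accordingly. If an allowance was built in, they cannot see what it was for or judge whether it was large enough.

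**Working it through.** **Inputs** (Sample size calculation section): p1 = 0.60, p2 = 0.75, two-sided alpha = 0.05, power = 0.80, drop-out = 10%, equal arms. Two readings are assumed. The 15% is taken as percentage points, and the 60% starting level is taken to persist under usual care at 24 months.

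**Formulas.** With d = p2 − p1 and p̄ = (p1 + p2)/2:

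- Uncorrected: n = [z(1−α/2)·√(2p̄(1−p̄)) + z(power)·√(p1(1−p1) + p2(1−p2))]² / d²
- Continuity-corrected: n_c = (n/4)·[1 + √(1 + 4/(n·d))]²
- Enrolled = evaluable / (1 − 0.10)

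**Step 1. The plan as stated (80% power).**

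- p̄ = 0.675, √(2 × 0.675 × 0.325) = 0.6624, and √(0.24 + 0.1875) = 0.6538.
- n = (1.960 × 0.6624 + 0.8416 × 0.6538)² / 0.0225 = (1.2982 + 0.5503)² / 0.0225 = 151.9, so 152.
- n_c = 164.9, so 165.
- Enrolled: 152/0.9 = 168.9, so **169**; 165/0.9 = 183.3, so **184**.
- Compared with the stated figure: 240/169 = 1.42 and 240/184 = 1.30. The plan's 240 is not reproduced.

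**Step 2. Other readings at 80% power.** An unpooled variance gives 167 enrolled, and the arcsine method gives 169. For 60% versus 45% the result is at most 207. Across all pairs of proportions 15 points apart, the requirement peaks near 50% (42.5% versus 57.5%) at 187 evaluable continuity-corrected, and 187/0.9 = 207.8, so 208 enrolled. No reference rate combined with a 15-point difference reaches 240, so the use of a starting level instead of a 24-month usual-care rate cannot explain the gap.

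**Step 3. Power at the stated size.** 240 × 0.9 = 216 evaluable per arm. With no other inflation, power for 60% versus 75% is 91.7% uncorrected and 90.0% continuity-corrected.

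**Step 4. Routes that do give 240.**

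| Route | Evaluable per arm | Enrolled per arm |
|---|---|---|
| 90% power, alpha 0.05, uncorrected | 203 | 226 |
| 90% power, alpha 0.05, continuity-corrected | 216 | **240** |
| 80% power, alpha 0.05/3, continuity-corrected | 216 | **240** |
| 80% power, alpha 0.05, uncorrected, design effect 216/152 = 1.42 | 216 | **240** |
| 80% power, alpha 0.05, continuity-corrected, design effect 216/165 = 1.31 | 216 | **240** |

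The second and third rows agree because both give n_c = 215.9 before rounding up. Every route that reaches 240 needs at least one element that the article does not state.

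**The case against.** The strongest defence is that the surplus was deliberate. The Data analyses section expects clustering, the Discussion expects contamination between arms that would dilute the effect, and there are three sub-studies. A modest allowance for any of these could have led from 152 or 165 to 216 evaluable. The document is also a condensed article, so the formula and any inflation may be in the full protocol. This stands as a reason not to name a cause. It does not remove the finding, because the sentence presents 240 as following from inputs that do not give it. The multiplicity route also conflicts with the 5% level stated both for the sample size and for the primary test.

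A second defence is that the discrepancy is conservative, and that a null result will be read mainly from its confidence interval. That stands too, and it limits the severity.

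Three stronger readings are tempting, and the article does not support them.

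- *The power should read 90%.* The match is exact, but only with a continuity correction that the article does not mention (226 without it), and other routes match equally well.
- *Each sub-study has ample spare attrition.* On the bare formula, 80% power would survive losses of 1 − 165/240 = 31% to 1 − 152/240 = 37%. That holds only if the surplus was not already committed to clustering, contamination or multiplicity.
- *The 15% may be relative, or in HbA1c units.* The wording is loose, but the sentence before it defines the measure as a difference in proportions, and the section repeats that the outcome is a percentage of people. The percentage-point reading is the natural one.

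**Conclusion.** The point holds as an internal contradiction in the sample-size statement. At 80% power the stated inputs need 169 per arm, or 184 with continuity correction, and the stated 240 is 30% to 42% above that. As written, and with no hidden inflation, the size corresponds to about 90% to 92% power. The mismatch itself does not depend on the 60% reference rate, since no pair of proportions 15 points apart needs more than 208. The power figures do rest on 60% versus 75% with 216 evaluable per arm.

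Which element is wrong cannot be determined from the article. The 90%-power route is one good candidate and is not proven. No sub-study is underpowered on its own assumptions, and the enrolment target, endpoint and test are unaffected. Severity is moderate: a reporting correction to a figure that all three sub-studies rely on.

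**What to change.** Retrieve the original calculation and rewrite the sentence so that its inputs reproduce 240.

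- **If no inflation was used:** state 60% versus 75% (15 percentage points, absolute), two-sided 5%, 90% power, continuity-corrected, 216 evaluable and 240 enrolled per arm after 10% drop-out.
- **If an allowance for clustering, contamination or multiplicity was used:** keep 80% power and state the allowance, its size and the formula. If it was a reduced alpha, reconcile it with the 5% level given for the primary test in the Data analyses section.

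In either case, describe the 15% as percentage points in the proportion with controlled HbA1c. The 90% wording should not be printed before the check, because it would be a new error if the surplus was an allowance. The cost is a look at the original calculation and a change of wording. Enrolment stays at 240 per arm and 480 per country.

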### Enrolment of participants

Eligible are people above 18 who have been diagnosed with diabetes based on the WHO/IDF guidelines who are listed in a centre participating in the study and have received at least one session with an educator in the DSME programme in the last year. There are no additional exclusion criteria. All people in the participating centres, patients and staff, will be informed about the study through announcements, written materials and meetings and they will be invited to participate. In DRC and Cambodia , enrolment is carried out in a serial way, during consecutive days planned for each participating centre. Because of the smaller size of the educator’s groups, enrolment in the Philippines will be done in a droplet way. The randomisation system uses a 4X4 block randomised block design with the participant as unit of randomisation. Study code numbers and randomisation envelopes are prepared prior to enrolment. Persons willing to join will be subject to an informed consent procedure. After signing the informed consent form, they will be assigned a code number and be allocated to either trial arm. This procedure will be led by the study team, independently from the staff in the participating centres. Randomisation is blinded, but the nature of the intervention leads participants to know to which arm they belong. Educators and other staff of the participating centres may get to know this information through the participants as well.

### Usual care: the diabetes self management education programme

The project introduces a DSMS intervention in addition to an existing DSME programme. Before the DSMS intervention starts, all country teams will have optimised their existing DSME-programme up to the level of a ‘minimum package’. This comprises a coherent story explaining diabetes for patients and key messages about nine specific dimensions of disease management: 1) explanation of diabetes; 2) healthy eating; 3) physical activity; 4) monitoring; 5) medications; 6) foot care; 7) tobacco and alcohol control; 8) patient-held records; and 9) problem solving by and empowerment of patients [31,32]. The minimum package has been defined through a consultation process with people from the existing DSME projects and with diabetologists providing expert advice. The minimum package is locally validated and fine-tuned to the local context by each country team, in collaboration with local project staff, health care providers and patients. There will be a written curriculum of the DSME programme in each country.

### Intervention

The content and process of DSMS is based upon the minimum DSME package and on elements of behaviour theory, aiming to influence the modifying factors of behaviour. DSMS messages can, for instance, increase knowledge about certain behaviours and their effects, they can create normative beliefs and social pressure and they can provide emotional support and increase the perception of control by people with diabetes. Messages for DSMS will follow the nine dimensions of DSME, but will be locally developed and validated through consultations with DSME staff and people with diabetes. The local validation pertains to the local meaning of health behaviours (for instance what is a healthy diet) but also to locally relevant modifying factors of behaviour (constraints for doing physical exercise). The participants allocated to the intervention group will receive a regular mobile phone. They will receive standardised and individualised Project-Initiated Communication (ProjIC) through Short Messaging Services (SMS), which implies the maximum length of messages being 160 characters. The software FrontLine is used to send SMS in an convenient way. Furthermore, people are encouraged to use the phone to contact other people including fellow patients, educators and providers to ask for advice or provide information when needed, for instance when they cannot come to an appointment. Depending on the arrangements with the national telephone providers, participants will be provided with a budget for calls and messages. This is termed Patient-Initiated Communication (PatIC).

To control for the potential effect of providing participants with a regular mobile phone, the participants allocated to the usual care group will also receive a mobile phone but will not receive ProjIC. They will however continue to receive assistance from their educators according to the DSME programme.

The educators are not involved in the initiation of DSMS-related communication. However, all educators will be provided with a regular mobile phone so that they can be reached by patients. They will receive a modest monthly allowance to compensate them for the additional work and costs that they will have because of the intervention: receiving more calls/SMS from patients; taking necessary action upon these; and being involved in the data collection for physical examination and blood sampling. They will continue to provide DSME to their patients irrespective of their allocation to one of the trial arms.

The study project manager in each country is the central person in providing ProjIC to the people in the DSME+DSMS group. He/she will be provided with a smart phone with instructions and training on how to use it. He/she will enter patient-related data into a database that is developed and managed at national level and send out ProjIC to patients that belong to the DSME+DSMS group in the different participating centres/field sites. He will support and give feedback to educators when necessary and coordinate research data collection at site level.

